## SUMMARY AND GENERAL INFORMATION

|  |             |
|--|-------------|
|  | exact test) |
|--|-------------|

## 0.4 Flowsheet

[figure not shown]

**Schedule of CT, FDG-PET and FLT-PET imaging**

| Time point                      | Imaging of involved areas |
|----------------------------------------|----------------------------------|
| Between d-10 and d1 (prior to therapy) | FDG-PET, FLT-PET, CT             |
| Day 1                                  | Start of therapy with erlotinib  |
| Between d7 and d14                     | FDG-PET and FLT-PET              |
| Week 7                                 | FDG-PET, FDG-PET, CT             |

## 1 STUDY DESIGN: RATIONALE

### 1.1 Systemic treatment options in NSCLC

Non small cell lung cancer (NSCLC) is the leading cause of cancer death in the western world (Jemal et al., 2004). While only a minority of patients with early stage disease is cured by radical surgery, most patients present with locally advanced or metastatic disease (stage IIIB, stage IV). None of these patients will be cured and the overwhelming majority dies within the first year after diagnosis. Chemotherapy has been shown to increase survival and to improve quality of life in these patients. However, the increase in median survival time is marginal, i.e. in the range from 2 to 4 months corresponding to an increase in the 1 year survival rate in the range from 10 – 20% (Spira and Ettinger, 2004). In patients with a good performance state the administration of a standard two drug chemotherapy regimen, not necessarily being platinum-based (D'Addario et al., 2005), is considered standard treatment. No significant differences could be observed between several of such standard regimens (Schiller et al., 2002). Similar effects, however, have also been demonstrated in older patients with monochemotherapy alone. Recently, in a large randomized trial the addition of the monoclonal anti-VEGF antibody bevacizumab to paclitaxel/carboplatin first line chemotherapy has been shown to cause an overall survival benefit of two months in non squamous cell NSCLC (Sandler, 2005). Nearly all patients suffer from relapse of the disease with a median survival time of only a few months following diagnosis of relapse. Several chemotherapeutic agents, among others docetaxel, gemcitabine, vinorelbine, exert therapeutic activity in these patients and even a moderate effect on survival compared to best supportive care could be shown for docetaxel (Shepherd et al., 2000). In addition, the new multitargeted antifolate pemetrexed exerts a therapeutic activity comparable to docetaxel, however, with a better tolerability (Hanna et al., 2004).

### 1.2 EGFR-targeted therapy in NSCLC

The disappointing results of chemotherapy stimulated an intense search for new therapeutics in NSCLC. The knowledge of the particular changes in molecular signaling pathways involved in malignant transformation and tumor progression has led to the generation of novel drugs ("biologicals") that specifically target at signaling intermediates of oncogenic pathways (e.g. small-molecule inhibitors of tyrosine kinases) or growth factor receptors on the cell surface (e.g. monoclonal antibodies). Several of these drugs have already been established in other solid tumors. Well-known examples are the monoclonal antibody (Mab) trastuzumab targeting HER2 in HER2-expressing breast cancer (Cobleigh et al., 1999) and the tyrosine kinase inhibitor (TKI) imatinib mesylate in chronic myelogenous leukaemia (Druker et al., 2001). In NSCLC the epidermal growth factor receptor (EGFR) represents an attractive target for such innovative drugs. The EGFR (HER1) is a member of the HER growth factor receptor family of tyrosine kinases. Activation of this receptor tyrosine kinase activates an intracellular signal transduction cascade with effects on cell growth, survival, angiogenesis and differentiation. The EGFR pathway is thus regarded as pivotal for the regulation of malignant growth in several cancers, among them NSCLC (Yarden, 2001). Three EGFR-targeted "biologicals" have already shown therapeutic benefit in NSCLC, i.e. one monoclonal antibody and two small-molecule tyrosine kinase inhibitors. The Mab cetuximab (ErbixR), which recently has received FDA approval for treatment of relapsed

colorectal cancer, has been shown to improve response rates in NSCLC when added to platinum-based chemotherapy (Gatzemeier, 2003). The two oral TKI gefitinib (IressaR) and erlotinib (TarcevaR) induce clinical responses in about 10% of relapsed NSCLC patients and stable disease in about 40% (Fukuoka et al., 2003; Kris et al., 2003; Shepherd et al., 2005). Chemotherapy-typical toxicity is avoided with acne-like skin lesions and diarrhoea representing the most prominent side effects. Recently, in a phase III multicenter trial of the National Cancer Institute of Canada a survival benefit was reported for relapsed NSCLC patients treated with erlotinib with a median survival time of 6.7 months (placebo: 4.7 months; (Shepherd et al., 2005). By comparison, despite impressive clinical responses in a subset of patients, no overall survival benefit in patients with relapsed NSCLC could be shown for gefitinib compared to placebo in a recently published randomized trial (Barge, 2004). Gefitinib had already received approval for the treatment of NSCLC patients after two chemotherapeutic treatment regimens in the USA, Japan, Australia and Switzerland due to the impressive clinical responses. But, until the final analysis of the data of the ISEL trial and further ongoing trials the administration of gefitinib is no more recommended (Barge, 2004). In the US and in the EU, erlotinib is approved for therapy of relapsed NSCLC after failure of at least one chemotherapy. Recently, first-line treatment of NSCLC patients in advanced stage (IIIB/IV) with erlotinib was evaluated in a phase II study and impressive clinical responses were reported. The non-progression rate was 55%. Best response was: 1 CR, 12 PR, 16 SD, 17 PD, 7 NE in this cohort (Giaccone, 2005). Furthermore, Jackman and colleagues performed a study in elderly patients with erlotinib monotherapy as a first line treatment. Efficacy was demonstrated with median 1 year survival rate of 46% and a median overall survival of 10.9 months comparable to results expected in the firstline treatment with combined platinum based chemotherapy (Jackman et al., 2007) (Schiller et al., 2002). In a German study using gefitinib monotherapy in the first line setting the progression free survival was described as 7 weeks (Reck et al., 2006). Further studies to test erlotinib in the line setting progression free survival are ongoing.

### **1.3 Correlation of EGFR/ KRAS mutations and EGFR immunohistochemistry to clinical benefit**

Mutations in the EGFR (frequency 2-25%) correlate with response (partial response, complete response) to EGFR-TKI (Lynch et al., 2004; Paez et al., 2004) in patients with NSCLC. These mutations were found within the kinase-domain-encoding region of the EGFR gene in tumor DNA of erlotinib and gefitinib responders, but not in that of non-responders. These results suggest that the kinase domain mutations may lead to enhanced binding of erlotinib and gefitinib in the ATP-binding pocket of the kinase domain, and thus, to enhanced inhibition of the tyrosine kinase and, ultimately, to enhanced tumor control. The kinase domain of the EGFR gene is encoded by seven exons and can reliably be detected in the tumor tissue only when the tumor-cell population represents more than ~70% of the affected tissue.

Protein expression of EGFR assessed by immunohistochemistry has been demonstrated to be predictive for clinical response to treatment with either gefitinib or erlotinib (Cappuzzo et al., 2005; Shepherd et al., 2005).

Interestingly, there is a group of patients without mutations within the EGFR also responding to inhibition with EGFR-TKI (Pao et al., 2004). In addition, a substantial proportion of patients

treated with EGFR-TKI experience a clinical benefit by achieving a stable disease state which is not correlated to EGFR mutations. Moreover, in the randomized trial (Tarceva vs. placebo) the survival benefit for patients with Tarceva was not correlated to EGFR mutational status (Shepherd et al., 2005; Tsao, 2005). Thus, although EGFR mutations are highly correlated to response to EGFR-TKI, they do not predict clinical benefit and survival.

Mutations within KRAS have a negative prognostic impact on clinical outcome in NSCLC (Rodenhuis and Slebos, 1990). Activating mutations within the KRAS gene are found in 15-50% of lung adenocarcinoma and are mostly localized within exon 2 (Rodenhuis et al., 1988; Suzuki et al., 1990). It has recently been shown that mutations within KRAS confer resistance to the treatment with erlotinib and gefitinib and are mutually exclusive with EGFR mutations (Pao et al., 2005). Based on their low frequency of about 15% and a 50-60% progressive disease rate it is well conceivable that KRAS mutations do not represent the only determinant of resistance to erlotinib respectively gefitinib treatment.

Taken together, sequence analyses of EGFR or KRAS for pre-treatment prediction of clinical response will likely miss a subset of responders that might have experienced substantial clinical benefit from EGFR-targeted therapy (i.e. non-mutated responders). Further the mutational status of those patients with stable disease is not yet clear. Moreover, these analyses are presumed to be only rarely applicable in clinical routine diagnostic procedures. So far, no assays are available that identify those patients definitely not profiting from EGFR-TKI treatment, i.e. patients with progressive disease under treatment.

#### **1.4 FDG- and FLT-PET for assessment of response to treatment**

The addition of FDG (fluoro-deoxy-glucose)-PET to conventional pre-treatment workup has now become part of the guidelines of the American Society of Clinical Oncology (ASCO) for the diagnostics of patients with lung cancer (Pfister et al., 2004). This is due to an increase in specificity and sensitivity as compared to conventional CT scans (Pieterman et al., 2000; van Tinteren et al., 2002). In addition, substantial progress in measurement of tumor cell proliferation by PET has been made by synthesis of FLT (fluoro-L-thymidine, (Shields et al., 1998). FLT is trapped in tissue after phosphorylation by thymidine kinase 1 (TK1), resulting in high accumulation in tumors compared to non malignant tissue. In NSCLC, a high correlation was found between standardized uptake value (SUV) measures of FLT uptake and Ki-67 scores, an established marker of tumor cell proliferation (Buck et al., 2003; Buck et al., 2002). In these studies, the specificity was 100% and the sensitivity was ~85%. These findings suggest FLT-PET to become an ideal complementary technology to FDG-PET due to its higher specificity. Here, we hypothesize that a decrease in tumor cell proliferation as an early event during the response to erlotinib may be visualized by FDG- and/or FLT-PET and, vice versa, absence of this response may predict early progress. This hypothesis is mainly built on the following findings: Tumor cell proliferation was rapidly reduced by erlotinib in an in-vitro model of lung adenocarcinoma (Pao et al., 2004). Since at least FLT-PET was shown to directly correlate to tumor cell proliferation (Buck et al., 2003; Buck et al., 2002), we assume that FDG-/FLT-PET will allow to early determine response status of a patient under erlotinib treatment. Further clinical and experimental data support our hypothesis: In several early clinical studies it has been demonstrated for different malignancies such as breast cancer (Rousseau, 2005), soft tissue sarcoma (Schuetze, 2005), glioblastoma (Charnley NG, 2005), rectum cancer (Di Fabio, 2005) and lung cancer (Griesinger, 2005; Schmuecking,

2005) that clinical response to chemotherapy can be detected by FDG-PET after 4-8 weeks. Sensitivity for response prediction outperformed conventional imaging in these studies. In squamous cell cancer of head and neck it has been demonstrated that FDG-PET after completion of treatment with an anti-EGFR antibody depicts response consistently (L Bastholt, 2005). Furthermore, not only response to treatment, but also clinical progression can be detected reliably by FDG-PET in mesothelioma (Kimura, 2005). In an in vivo model of fibrosarcoma Leyton and colleagues detected a decrease in FLT uptake as early as 24h after start of chemotherapy with cisplatin. In this model FLT outperformed FDG as tracer (Barthel et al., 2003; Leyton et al., 2005). Similar data were obtained in an allograft mouse model of a squamous cell tumor as well as an cervical adenocarcinoma model (Sugiyama, 2004). Moreover, in recent studies FDG-PET was shown to reliably predict early response of patients with gastrointestinal stromal tumors (GIST) to the small molecule tyrosine kinase inhibitor imatinib mesylate or SU11248 (Jager et al., 2004; Stroobants et al., 2003; van den Abbeele, 2005) on day 8. Also response of GIST to treatment with the mTOR inhibitor AP23573 can be detected by FDG-PET already on day 5 of treatment (Sankhala, 2005).

## 2 AIM OF TRIAL

Based on the survival benefit demonstrated in patients with relapsed NSCLC (Shepherd et al., 2005) as well as on its favourable toxicity profile compared to chemotherapy the EGFR-TKI erlotinib represents an attractive candidate to be included also in protocols for the first line treatment of NSCLC. Accordingly, preliminary data from phase II trials show promising response rates for erlotinib treatment in the first line setting (Giaccone, 2005). In parallel, in the near future further targeted drugs will be available for NSCLC treatment. For instance, the addition of the anti-VEGF monoclonal antibody bevacizumab has recently shown to prolong survival when added to standard chemotherapy as first line treatment of NSCLC. Thus, in order to optimize the choice and the sequence of new drugs in NSCLC treatment, an early identification of patients with no clinical benefit, i.e. patients with progressive disease under treatment, is desirable. In the ERLOPET trial, we aim at establishing PET analysis as a tool for early identification of NSCLC patients with no clinical benefit from monotherapy with erlotinib as first line treatment. A pre-treatment computed tomography (CT) scan will be performed for evaluation of the patients' individual tumor burden. FDG- and FLT-PET scans will be performed between d -10 and d1 (but prior to therapy) for identification of pre-treatment PET status. Between d7 and d14, FDG- and FLT-PET scans will be performed for the early identification of erlotinib non responders. The imaging procedures will be performed at different days, i. e. one procedure per day. After six weeks of treatment, final response evaluation will be performed using CT, FDG- and FLT-PET scans. These results will be correlated to the mutational status of the EGFR - and the KRAS gene and the expression of EGFR in pretreatment samples.

### **3 TRIAL PLAN**

#### **3.1 Trial design, primary and secondary objectives**

##### **Design**

Phase II study (therapeutic exploratory), single center, single arm, open-label

##### **Primary Objective**

To evaluate the accuracy of FDG-/FLT-PET analyses for early prediction of erlotinib non-response in patients with stage IIIB/IV NSCLC (measured by ROC analysis of the SUV) treated with erlotinib

##### **Secondary Objectives**

1. To identify PET characteristics for progressive disease following erlotinib treatment (changes in SUV during treatment)
2. To identify PET characteristics for response to erlotinib (changes in SUV during treatment)
3. To identify PET characteristics for stable disease following erlotinib treatment (changes in SUV during treatment)
4. To confirm the statistical association of EGFR mutational status and clinical response in NSCLC patients treated with erlotinib
5. To confirm the statistical association of KRAS mutational status and clinical resistance to treatment of NSCLC patients with erlotinib
6. To determine the discriminatory capability of FDG-/FLT- PET regarding EGFR and KRAS mutational status in NSCLC patients
7. To compare prognostic value of FDG-PET, FLT-PET and EGFR mutational status regarding clinical response in NSCLC patients treated with erlotinib
8. To identify EGFR and KRAS sequence characteristics for clinical response and stable disease following erlotinib treatment
9. To assess safety of Erlotinib
10. To determine response rates
11. To determine rates of stable diseases
12. To determine one-year FFTF
13. To determine one-year OS
14. To determine median overall survival time

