#### **3.2 Recruitment**

It is planned to recruit a maximum of 40 patients over a 15 months period.

Patients will be recruited after screening only if all inclusion criteria are met, no exclusion criteria are met and written informed consent has been obtained. No difference in recruitment concerning gender will be applied. According to the distribution of NSCLC more male than female study participants are expected.

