## Analysis of secondary endpoints

The prognostic value/accuracy of FDG/FLT-PET regarding clinical failure, SD and clinical response in NSCLC patients treated with erlotinib will be compared by ROC analysis; optimal cut-off values for FDG/FLT PET will be chosen (*secondary objective*).

Association between EGFR mutation, KRAS mutation and EGFR positivity with clinical response will be tested by Fisher's exact test.

Secondary endpoints (FFTF and OS) will be analyzed using descriptive statistics after at least one year follow-up of all patients.

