## 7.3 Further analyses

### Subsequent analyses

### Expected results

Based on the results of clinical trials with erlotinib in NSCLC patients in Western Europe and the US, we expect about 10% of patients with response (CR, PR) to treatment with erlotinib, about 30% with stable disease and about 60% with progressive disease. Furthermore, we expect about 90% of patients with mutated EGFR responding to therapy. KRAS mutations and EGFR mutations are expected to be nearly exclusive.

Based on published PET data, especially from patients with GIST treated with imatinib, we expect a nearly 100% association of clinical response (CR, PR in CT after 6 weeks of treatment) and reduction in SUV (PET analyses on days 8,9).

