## Sample size calculation

Assumptions:

- (1) 10% responder, 60% progressers; thus 40% non-progressers
- (2) Primary variable is the 'area under the ROC curve (AUC,  $\vartheta$ )', (PET-values of non-progressers > progressers)
- (3) Variability in the PET-results of non-progressers is greater than that of progressers
- (4) Type-I-error 0.05; type-II-error 0.20
- (5) True accuracy (AUC) is at least 0.70 (alternative hypothesis; some common diagnostic tests have an AUC greater than 0.70 [1; p29])

Sample size calculation:

| AUC ( $\vartheta$ ) | # Non-progressers | # progressers | # Total   |
|---------------------|-------------------|---------------|-----------|
| 0.70                | 26                | 38            | 64        |
| 0.75         | 16         | 24     | 40 |
| 0.80                | 11                | 16            | 27        |

Note: The sample size was calculated using formulae (6.3) and (6.6) in [Zhou et al., 2002; p199, 201].

Thus, assuming  $\vartheta_1 = 0.75$ , 40 patients are needed to reject the null hypothesis  $H_0: \vartheta = 0.5$  in favour of the alternative  $H_1: \vartheta \neq 0.5$ . The sample size will be sufficient to yield a 95% confidence interval for  $\vartheta$  with width  $2 \times 0.17 = 0.34$ .

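### The FDG v FLT ROC comparison on clinical response rests on about 4 responders and near-perfect expected accuracy, where the named method gives zero or far too narrow error bars

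*Protocol*

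**What the plan says.** Item 7 of the secondary objectives (sections 3.1 and 7.1) reads "To compare prognostic value of FDG-PET, FLT-PET and EGFR mutational status regarding clinical response in NSCLC patients treated with erlotinib". The protocol uses response for CR and PR, and non-progression for CR, PR and SD together.

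Under Analysis of secondary endpoints in section 7.2, the accuracy of FDG/FLT-PET for clinical failure, SD and clinical response "will be compared by ROC analysis; optimal cut-off values for FDG/FLT PET will be chosen". Section 7.4 names the DeLong nonparametric method for the ROC analysis. For EGFR mutation, KRAS mutation and EGFR positivity, section 7.2 gives only Fisher's exact test of association with response.

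The expected data are set out in three places:

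- Section 3.2: "It is planned to recruit a maximum of 40 patients over a 15 months period".
- Section 7.3, Expected results: "we expect about 10% of patients with response (CR, PR) to treatment with erlotinib"; "we expect a nearly 100% association of clinical response (CR, PR in CT after 6 weeks of treatment) and reduction in SUV"; and "we expect about 90% of patients with mutated EGFR responding to therapy".
- Section 7.3, Sample size calculation: "10% responder, 60% progressers; thus 40% non-progressers".

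No power is claimed for objective 7, and the trial is labelled therapeutic exploratory.

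**The concern.** The outcome, its expected frequency, the expected accuracy of PET and the ROC method are all stated in the protocol, and they do not fit together. DeLong standard errors are built from the spread of each patient's placement among patients of the other group. With about 4 responders almost perfectly separated from the rest, there is little or no spread to measure.

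Two misreadings could follow. A perfectly separated sample gives an AUC of 1 with an interval from 1 to 1, which looks like certainty. If both tracers do this, or nearly so, the absence of a difference could be read as equal value when it only reflects how few responders there were.

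**Working it through.** **The plan's own figure.** The primary sizing reproduces. Use V = 0.0099·exp(−A²/2)·[(5A²+8) + (A²+8)/R], with A = 1.414·Φ⁻¹(AUC), R = 24/16 = 1.5, two-sided α of 0.05 and 80% power.

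- V at AUC 0.5 is 0.132; V at AUC 0.75 is 0.116.
- n = [1.96·√0.132 + 0.84·√0.116]² / 0.25² ≈ 16 non-progressers, and 1.5 × 16 = 24 progressers.
- Half-width = 1.96·√(0.116/16) ≈ 0.167, matching the stated 0.17.

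This sizing concerns non-progression only and does not carry over to clinical response.

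**Number of responders.** 10% of 40 = 4, leaving 36 others. With a binomial count (n = 40, p = 0.10), P(≤1) = 8.0%, P(≤2) = 22% and P(≤3) = 42%.

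**Why the variance vanishes.** The DeLong variance of an AUC is S₁₀/m + S₀₁/n. S₁₀ is the sample variance, over the m responders, of the share of non-responders each one exceeds. S₀₁ is the mirror quantity over the n non-responders. With complete separation every share equals 1, so both terms are 0. If both tracers separate completely, the variance of their difference is also 0 and the test statistic is 0/0.

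**How often.** The protocol gives no AUC for response, so the values below are assumptions. The simulation uses binormal PET values, 4 v 36 patients and within-group FDG-FLT correlation 0.5.

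| Assumed AUC, both tracers | Zero variance of the FDG-FLT difference |
|---|---|
| 0.95 | about 5% |
| 0.98 | about 21% |
| 0.99 | about 39% |

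A second simulation let the responder count vary, with correlation 0 or 0.6, and also counted trials with fewer than 2 responders as undefined. The undefined share was 12-17% at AUC 0.95, 41-47% at 0.99 and 84-87% at 0.999. The FDG v FLT test was significant in at most 2%.

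**Interval for one AUC (4 v 36).** Nominal 95% DeLong intervals cover the true AUC about 75% of the time at 0.90, 67% at 0.95 and 42% at 0.99.

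**What an exact method reports instead.** If all 4 responders and none of the 36 others are flagged, the lower exact 95% limit is 0.025^(1/4) = 0.398 for sensitivity and 0.025^(1/36) = 0.903 for specificity. Sensitivity is then 40% to 100%, where DeLong gives an AUC interval of zero width.

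**If the tracers really differ.** For AUC 0.90 v 0.75, power is about 22% with 4 v 36 and about 52% with 16 v 24.

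**The case against.** Several points on the other side stand.

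- **No test is stated for this comparison.** Section 7.2 attaches a level to the primary AUC test and the Fisher tests, not to the secondary ROC comparison. The AUCs can be reported even when the standard error is zero. So it would be too strong to say the comparison cannot be computed; what fails is the uncertainty attached to it.
- **The PET AUC is an assumption.** Section 7.3 ties response to a fall in SUV but does not say that patients with stable disease show none. If they do, the AUC for CR/PR against the rest need not be near 1. At 0.95 the zero-variance share is only about 5%. Interval coverage is still poor there, and at 0.90.
- **The response rate may be higher.** The first-line study cited in section 1.2 had 13 responders of 53 (24.5%), which would give about 10 in 40. FDG v FLT would still be undefined in 16-22% of trials at AUC 0.99 and 71-76% at 0.999.
- **Low power for an unsized exploratory objective is a limitation, not an error.** Response is also a legitimate outcome on which to compare PET with EGFR status, so objective 7 need not be replaced.

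A reader might go further and infer that PET and EGFR status can almost never be separated either. The protocol does not support this. It assigns EGFR to Fisher's exact test and states no ROC comparison of PET with EGFR. Its 90% is the response rate among mutated patients, not a sensitivity. With 10% responders, sensitivity is 0.9 × (mutation frequency)/0.10: 0.90, 0.45 and 0.18 at frequencies of 10%, 5% and 2% (section 1.3 gives 2-25%). A nominal DeLong test of PET v EGFR would be significant in about 1-2%, 32-44% and 45-65% of trials respectively, though with equal AUCs of 0.59-0.72 that test rejects 12-14% of the time at a nominal 5%.

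**Conclusion.** The point holds for the two tracers on clinical response. In the situation the protocol itself predicts, the named method gives a zero variance for the FDG-FLT difference in about 5-39% of trials, and single-AUC intervals covering about 42-67% instead of 95%. These figures assume AUCs of 0.95-0.99, binormal values, within-group correlation 0.5, exactly 4 v 36 patients and no missing scans. Higher AUCs make matters worse; a response rate nearer 25% eases them without removing the problem.

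It does not extend to PET v EGFR, it is not a complaint about power, and the primary analysis on non-progression is unaffected. It is a minor but cheaply avoided weakness in a secondary analysis.

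**What to change.** 1. Keep objective 7 on clinical response and label it descriptive. For FDG, FLT and EGFR status, give the cross-table against CR/PR and the sensitivity and specificity with exact 95% intervals. Report no DeLong test or interval on this outcome. Exact intervals presume a cut-off not chosen from the same few responders, so fix the PET cut-off beforehand or state that its selection is not reflected.
2. Add a comparison of FDG, FLT and EGFR status on non-progression (about 16 v 24), the trial's primary outcome, and state how the binary EGFR result enters it.

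The cost is protocol or SAP wording and one further analysis; no new patients or scans. There is no longer a formal test on clinical response, and power on non-progression remains modest, at about 52% for AUC 0.90 v 0.75.
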